### Outcome Measures of Heart Rate Variability

Interbeat time interval (R-R) variation will be used to determine the autonomic modulation using Firstbeat Bodyguard equipment (Firstbeat Technologies, Jyväskylä, Finland). This device will be used to record HRV data for 20 min (at rest and during ICT application). Recordings will be exported from the devices to the computer via Firstbeat Uploader Software (Firstbeat Technologies) and analysed using Kubios Software (University of Eastern Finland, Kuopio, Finland). To calculate the autonomous balance, the HRV method based on the Poincaré plot will be used^32,33^. This software has proven to be extremely valid and capable of recording non-linear trends that are frequently present on R-R intervals of record^34^.

Time-domain variables:

- ***MeanHR (bpm):*** It corresponds to the interval between two beats (R peaks on the ECG).
- ***pNN50 (%):*** Percentage of consecutive RR intervals that differ by more than 50 ms from each other. A high value of pNN50 provides valuable information about high spontaneous heart rate (HR)^35^.
- ***Root Mean Square of the Successive Differences (rMSSD) (ms)***: The square root of the average of the sum of the differences squared between normal adjacent. It shows the degree of activation of the Parasympathetic Nervous System on the cardiovascular system. This parameter reports the short-term variations of the RR intervals. It is directly associated with short-term variability^35,36^.
- ***Min HR and Max HR (bpm)***: They indicate the minimum and maximum heart rate, respectively, using *N* beats.

Frequency-domain variables:

- ***Low-Frequency power (LF) (ms^2^):*** Situated between 0.04 and 0.15 Hz. In long-term recordings, it provides us with more information about the activity of the sympathetic nervous system (SNS)^35^.
- ***High-Frequency power (HF) (ms^2^):*** They are located between 0.15 and 0.4 Hz. HF is clearly related to the activity of the parasympathetic nervous system (PNS) activity and has a relaxation-related effect on HR^35^.
- ***Low/high-Frequency ratio (LF/HF):*** From the low-frequency and high-frequency ratios of the HRV spectral analysis results we can estimate the vagal (related to relaxation and HF) and sympathetic (related to stress and LF) influence. Thus, we can estimate sympathetic-vagal balance^35^.

Non-linear variables:

- ***SD1 (ms):*** Sensitivity of short-term variability of the non-linear range of the HRV. It is considered an indicator of parasympathetic activity^32^.
- ***SD2 (ms)***: Long-term variability of the non-linear range of the HRV. It is a diameter from the Poincaré plot which indicates the degree of longitudinal dispersion. It is thought to reflect long-term changes in RR intervals and it is considered an inverse indicator of parasympathetic activity^32^.
- ***Stress Score (SS) (ms)***: It is an index described by Naranjo-Orellana et al.^32^ to facilitate the physiological interpretation of the Poincaré plot. It is expressed as the inverse of SD2 diameter multiplied by 1000.It is considered directly proportional to the sympathetic activity in the sinus node.
- ***Sympathetic/parasympathetic ratio (S/PS):*** It is also described by Naranjo-Orellana et al.^32^, S/PS is expressed as the quotient of SS and SD1. It is considered to reflect autonomic balance - that is, the relationship between sympathetic and parasympathetic activity.

## Intervention

All intervention procedures will be conducted by the same physical therapist. Los participantes del grupo experimental (n=14) realizaron un programa de LGET based motor control exercises. de Posteriormente, recibieron una sesión de terapia manual combinada con electroterapia ICT denominada electro-masaje^13^. Completaron un total de 8 sesiones en 4 semanas. On the other hand, los participantes del control group (n=17) no recibieron ninguna intervención para determinar el curso natural de la enfermedad. Los sujetos continuaron con sus actividades habituales del vuelo de combate y ejercicio. Se les pidió que no tomasen medicación o buscasen tratamientos alternativos.

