# METHODS

## Study design

We propose to conduct a single-blind randomised clinical trial with concealed allocation, intention-to-treat analysis and in which the treatment allocation is not known to the evaluator and the statistical investigator. The study will be conducted in accordance with the recommendations of the CONSORT^18^. statements. The future study will be conducted in accordance with the Declaration of Helsinki.

All data will be collected in the same room, at a temperature of 22–25 °C. Always in the same order and under the same environmental conditions for all subjects, both before and after the intervention.

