## Sample size

G*power 3.1 software will be used to calculate the sample size required to detect changes in the primary outcome (NPRS scale and JPSE). The calculations will be based on the detection differences of 2.5 points in the NPRS (MCID (minimal clinically important difference) (estimated for a variance in patients with neck pain of 10 points)^40^, assuming a standard deviation (SD) of 2.5 points.

Assuming an effect size (F-test) of 0.27 for ANOVA: repeated measures, within-between interaction groups differences, an alpha level of .05, and power of 80%, a total sample size of 30 participants will be estimated. The sample will be inflated by 10% to account for potential dropouts, resulting in a final target sample size of 34. This calculation showed that a sample size of 17 participants per group will be needed for a confidence interval of 95%, with a power of 80%, assuming a bilateral significance of .05.

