## Statistical Analysis

A descriptive analysis will be performed for each of the variables. The normality of the variables will be evaluated using the Shapiro-Wilk test, which showed a normal distribution for all the variables and, thus, parametric tests will be appropriate. Data will be reported as mean # SD. The demographic and clinical variables of the groups at baseline will be compared using the chi-square test for categorical data and the independent-samples t-test for quantitative data. A 2-way repeated measure analysis of variance will be performed to analyse the interaction effects of time (at baseline and post-treatment) in the 2 intervention groups (experimental and control group). The independent and paired-samples t tests will be used for comparisons between and within groups, respectively. Furthermore, the effect size will be calculated through Cohen's d coefficient. A value above 0.8 will be considered high; 0.5 moderate; and lower than 0.2 will be considered low^41^. Significance level will be established at p < 0.05. Data analysis will be made with the statistic software SPSS version 26.0 (SPSS Inc., Chicago, IL, USA).

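### The protocol plans 17 per arm but reports 14 and 17 as already treated, never states the numbers randomised, and names tests that do not support its intention-to-treat promise

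*Protocol*

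**What the plan says.** Four sections of the protocol bear on this.

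- **Sample size** looks forward. It requires 30 participants, inflates this for 10% dropout to 34, and concludes that "a sample size of 17 participants per group will be needed".
- **Intervention** looks back, mostly in Spanish. For the experimental arm: "Los participantes del grupo experimental (n=14) realizaron un programa de LGET based motor control exercises", and then "Completaron un total de 8 sesiones en 4 semanas" (they completed 8 sessions in 4 weeks). For the comparator: "los participantes del control group (n=17) no recibieron ninguna intervención" (they received no intervention).
- **Study design** promises "concealed allocation, intention-to-treat analysis".
- **Statistical Analysis** states that "A 2-way repeated measure analysis of variance will be performed to analyse the interaction effects of time", with measurements at baseline and after treatment. Independent t tests compare groups and paired t tests compare times. The same section gives the outcome of the Shapiro-Wilk test as known and rests the choice of parametric tests on it.

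No section gives the number randomised to each arm or explains the 14.

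**The concern.** There are two linked problems.

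First, the arm sizes conflict. A reader cannot tell whether 14 is the number randomised, the number who finished, or text left over from another document. Measured against the plan, the whole shortfall is in the treated arm. In a trial of about 31 people, three participants are a sizeable part of one arm, and who they are decides whether an analysis covers everyone randomised. If treatment and a first look at the data did precede this text, the arm sizes and the choice of tests were not fixed in advance, and the document should say so.

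Second, the analysis principle and the named tests do not fit together. The only provision for dropout is the 10% inflation. That protects power, but it does nothing about bias from who is missing. Because the control arm is untreated, any dropout caused by the programme itself could occur only in the experimental arm.

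**Working it through.** **1. Arm sizes side by side**

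| Section | Experimental | Control | Total | Tense |
|---|---|---|---|---|
| Sample size | 17 | 17 | 34 | planned |
| Intervention | 14 | 17 | 31 | past |

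Difference: 34 − 31 = 3, all in the experimental arm.

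**2. The plan's own figure.** Inputs from Sample size: f = 0.27, within-between interaction, α = 0.05 two-sided, power 80%. From Statistical Analysis: 2 groups and m = 2 time points. The correlation ρ between the two measurements is not stated; 0.5 is assumed.

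- Noncentrality: λ = f²·N·m/(1 − ρ), with 1 and N − 2 degrees of freedom.
- At N = 30: λ = 0.0729 × 30 × 2/0.5 = 8.75, power 81.5%. The smallest N reaching 80% is 29, or 30 with equal arms.
- Dropout: 30/(1 − 0.10) = 33.3, rounded up to 34, or 17 per arm.

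The stated 30 and 34 therefore reproduce at ρ = 0.5. They depend strongly on ρ: the required N is 56 at ρ = 0, 40 at 0.3, 24 at 0.6 and 16 at 0.75.

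**3. Power with the arms as written.** The same effect expressed as a standardised difference in change is d = 2·√(f²·m/(1 − ρ)) = 2·√(0.0729 × 2/0.5) = 1.08. For 14 versus 17 the noncentrality is 1.08/√(1/14 + 1/17) = 2.99 on 29 degrees of freedom, and power is 82.4%. At 17 + 17 it is 86.3%.

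Range over ρ for 31 participants, ignoring the slight imbalance: 53.8% at ρ = 0, 69.0% at 0.3 and 98.4% at 0.75. The planned 30 moves in the same way (52.4%, 67.5%, 98.1%), so the uncertainty comes from ρ and not from the 14:17 split.

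**4. Whom the named tests use**

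- Repeated-measures ANOVA with two time points: needs baseline and post-treatment values.
- Paired t test: needs both values.
- Independent t test after treatment: needs the post-treatment value.

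Run on the data as collected, each leaves out anyone without a post-treatment value.

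**5. Loss, if 17 were randomised to each arm (an assumption).** Experimental 3/17 = 17.6%; control 0/17 = 0%; overall 3/34 = 8.8%.

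**The case against.** The strongest case on the other side is that this may be careless drafting. The Intervention section mixes two languages, and stray past tenses also occur under Myoelectric activity and Interferential current electromassage. The sentence about 8 sessions can be read as describing the regimen rather than defining completers. The protocol nowhere calls its analysis complete-case or per-protocol. The same tests could be run after imputation, and rules for missing values may sit in an SAP that is not at hand.

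Much of this stands, and it rules out several stronger readings that a reader might infer:

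- **That three treated participants were excluded and intention-to-treat has been broken.** No section says that 17 were randomised to treatment or that anyone was dropped. Randomisation of 31 as 14 and 17 fits the text equally well, and so does leftover wording.
- **That the loss exceeds the planned 10%.** That allowance applies to the total, and 8.8% lies within it. No limit per arm is stated.
- **That the effect would be overstated by a known amount.** If three missing participants gained nothing while 14 gained 2.5 points over control, the all-randomised effect would be 2.5 × 14/17 = 2.06, a gap of 0.44 points. The loss and the zero gain are both assumed. Nothing in the protocol indicates why anyone would be missing, so even the direction is unknown.
- **That 14 versus 17 leaves the trial underpowered at 76%.** That figure (76.4%) comes from a two-sample t test at d = 2.5/2.5 = 1.0. By the same test 15 + 15 has only 75.3%, so it does not measure the effect of the imbalance. It is also not the method behind the stated sample size.

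The objection does not remove the conflict between two figures in one document, or the gap between the stated principle and tests that, as written, cannot use everyone randomised.

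**Conclusion.** The point holds in two parts. The contradiction in arm sizes is plain on the page: 14 and 17 (31) in the past tense, against 17 and 17 (34) as a plan, with the numbers randomised never given. The normality result reported as already known suggests that data had been inspected before this text was written, but does not prove it. The intention-to-treat promise is not supported by the named tests as written; that it was broken is not shown.

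The possible differential loss of 17.6% against 0% rests wholly on the unstated assumption that 17 were randomised to the experimental arm. Power is not the problem on the protocol's own inputs: about 82% at 14 versus 17 with an assumed correlation of 0.5. The numbers should be settled before any result is interpreted.

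**What to change.** 1. State how many were randomised to each arm, and reconcile 14/17 with 17/17, giving reasons for any difference.
2. Correct the tense in Intervention and Statistical Analysis, or disclose that treatment and data inspection preceded the text.
3. Define the primary set as everyone randomised, in the arm allocated, whatever the number of sessions attended.
4. Make the main comparison a baseline-adjusted one of post-treatment values: ANCOVA with multiple imputation, or a mixed model with a common baseline mean.
5. Add one sensitivity analysis assigning no improvement to experimental participants with a missing post-treatment value. Step 4 alone is not enough. Under missing-at-random, those without a value are predicted from those observed in their arm, so in the illustration above the estimate would stay near 2.5 and not move to 2.06.
6. If power is restated for the actual numbers, name its inputs, including the correlation.

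The cost is protocol wording and modest extra analysis. No new measurements are needed beyond trying to obtain post-treatment values from anyone who stopped.

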### Cervical Laser guided exercise therapy (LGTE)

LGTE is defined as a type of therapeutic exercise that provides external feedback to exercise, achieving an improvement in range of motion and postural control in subjects with spinal pain.

According to Abdollahipour et al. and Chiviacowsky et al. the external focus fosters a kind of automatic control that enables unconscious and rapid control processes^17,37^. In addition, it favours meta-action coupling, which is relevant to the fighter pilot's routine tasks. The "Motion Guidance Clinician Kit" (Motion Guidance LLC, Denver, CO, USA) will be used to carry out the exercise programme. The kit has a panel and a laser guide for the correct execution of cervical movements. The laser shall be positioned by means of an elastic strap at the pilot's forehead. The panel will be placed at a distance of 1.5 metres, attached to the wall. The programme will consist of 4 exercises, which will progress in difficulty according to the tolerance achieved with the passing of the sessions: a) Maintenance of the position of the head (cervical stabilisation); b) Cervical flexion-extension; c) Right-left rotations; d) Right-left latero-flexions. Each exercise consists of 4 sets of 8 repetitions, except the first one, in which the head position is maintained by pointing the laser at the centre of the panel for 30 seconds (4 sets). Between each series there will be 10 seconds of rest. Subjects will start with the subjects seated on a stool, and then move to a standing position from the 3rd session onwards. From the 5th session onwards, the distance between the signals to be reached with the laser will be increased, with the aim of increasing the range of cervical movement in the 3 planes of space. The average time for the complete programme should not exceed 14 minutes. The interventions will be carried out in compliance with the recommendations of the CERT^38^ and TIDIER^39^ statements.

### Interferential current electromassage

Following the motor control exercise programme, interferential current electromassage (ICE) in cervical region will be added for 15 minutes. ICE technique simultaneously combines manual therapy and ICT13. A bipolar application, using a carrier frequency of 4000 Hz at constant voltage and an amplitude-modulated frequency of 100 Hz (Sonopuls 692®; Enraf-Nonius BV, Rotterdam, The Netherlands), will be administered. The physiotherapist in charge of the intervention, in contact with the sponges, performs the sequence of manual soft tissue therapy while administering the interferential current into the body through the skin^13^ in the areas of the neck, shoulders and scapulae. The sequence combines strokes, bilateral lowering of the shoulders and stretching of the neck-shoulder muscles (e.g. upper trapezius and levator scapulae).

A strong level of intensity perception will be reached, but without causing pain or discomfort, as well as obvious muscle contraction, although a slight vibration (fasciculation) was allowed. Two rubber electrodes (6 × 8 cm) inside spontex of equal size were used. The sponges will be moistened with warm water to avoid unpleasant sensations and to allow normal gliding on the skin. Some needles shall be prepared with hot water to moisten the sponges during the procedure, if necessary.

## Sample size

G*power 3.1 software will be used to calculate the sample size required to detect changes in the primary outcome (NPRS scale and JPSE). The calculations will be based on the detection differences of 2.5 points in the NPRS (MCID (minimal clinically important difference) (estimated for a variance in patients with neck pain of 10 points)^40^, assuming a standard deviation (SD) of 2.5 points.

Assuming an effect size (F-test) of 0.27 for ANOVA: repeated measures, within-between interaction groups differences, an alpha level of .05, and power of 80%, a total sample size of 30 participants will be estimated. The sample will be inflated by 10% to account for potential dropouts, resulting in a final target sample size of 34. This calculation showed that a sample size of 17 participants per group will be needed for a confidence interval of 95%, with a power of 80%, assuming a bilateral significance of .05.

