## Participants

Convenience sampling will be followed. The inclusion criteria will be: (i) fighter pilots (male and female) who, at the time of the assessment, are an instructor or student attached to the 23rd Wing of the Talavera Air Base, Air Force (FAE), Badajoz; (ii) fighter pilots diagnosed with flight-related neck pain according to the International Classification proposed by a NATO expert panel4; (iii) fighter pilots diagnosed with flight-related neck pain according to the International Classification proposed by a NATO expert panel; (iv) fighter pilots diagnosed with flight-related neck pain according to the International Classification proposed by a NATO expert panel5; a minimum perceived pain score of 3/10 on the Numerical Pain Rating Scale (NPRS) on the early morning assessment within 48 hours of the last flight; (iv) scores of ≥5 points on the Neck Disability Index (NDI), and a cervical positioning error of ≥4.5°^19^. Exclusion criteria shall be: (i) Personal Psychological Apprehension Scale (PPAS) score greater than 37.5^20^; (ii) contraindication to electrical stimulation; (iii) having received physiotherapy or any other routine medical care six weeks prior to data collection; (iv) any regular use of medications known to affect autonomic nervous system (ANS) function or pain perception, including opioids, antidepressants, benzodiazepines, anti-inflammatory drugs and beta-blockers, two weeks prior to participation in this study; and (v) being involved in ongoing medico-legal disputes.

- - 1. Numeric Pain Rating Scale

Numeric Pain Rating Scale (NPRS) is a 11-point numeric rating scale, where 0 denotes “no pain” and 10 denotes “the maximum bearable pain”. The minimum clinically important difference (MCID) for this tool have been established at 1.3 points and the minimum detectable change (MDC) at 2.1 points^9^, in individuals with neck pain. The NPRS is a valid scale with moderate test-retest reliability in this population (ICC: 0.76, 95% CI 0.51 to 0.87)^9,21^.

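### NPRS and JPSE share primary status without a success rule, only NPRS has sample-size inputs and JPSE is undefined, so 5% error together with 80% power is not supported

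*Protocol*

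**What the plan says.** All references are to the protocol; no SAP is at hand.

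- **Sample size, purpose:** the calculation is meant "to calculate the sample size required to detect changes in the primary outcome (NPRS scale and JPSE"). This is a singular primary outcome made up of two variables.
- **Sample size, inputs:** "The calculations will be based on the detection differences of 2.5 points in the NPRS", "assuming a standard deviation (SD) of 2.5 points". Nothing comparable is given for JPSE.
- **Sample size, test:** "Assuming an effect size (F-test) of 0.27 for ANOVA: repeated measures, within-between interaction groups differences".
- **Sample size, result:** "an alpha level of .05, and power of 80%, a total sample size of 30 participants will be estimated". This is raised to 34 (17 per group) for 10% dropout. The section describes the significance level as bilateral.
- **Statistical Analysis:** "Significance level will be established at p < 0.05". The section ranks no endpoints and gives no rule for combining two primaries.
- **Outcome measures:** NDI, PCS, TSK-11, surface EMG and HRV are described here, and NPRS under Participants. JPSE is described in neither place; the abbreviation occurs once in the protocol and is not expanded.
- **Nearest related text:** an entry threshold under Participants ("a cervical positioning error of ≥4.5" degrees), and cervical repositioning as one of the things to assess in specific objective 1. Objective 6 then commits to analysing the programme's effect on the assessed variables.

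**The concern.** A stated alpha and power refer to a particular claim of success. Here that claim is not fixed, because the text allows a positive trial to mean that NPRS or JPSE is significant, or that both are. The two rules have different error rates and different power, and the calculation matches neither: it is a single-endpoint calculation with NPRS inputs.

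If one primary is significant and the other is not, the trial could be called a success or a failure after the data are seen. Because JPSE has no stated method or scoring, its definition could also be settled at that stage.

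**Working it through.** **Inputs from the protocol.** f = 0.27; two groups; two time points (m = 2); alpha 0.05; N = 30; dropout 10%.

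**Assumptions, not stated in the protocol.** Repeated-measures correlation rho = 0.5; sphericity correction 1; for joint power, JPSE also has f = 0.27.

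**1. Reproduce the plan's figure (one endpoint).** Noncentral F for the within-between interaction, with lambda = f² × N × m / (1 − rho), df1 = 1 and df2 = N − 2.

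- N = 30: lambda = 0.0729 × 30 × 2 / 0.5 = 8.75; power 81.5%.
- N = 28: power 78.5%. The smallest even N reaching 80% is therefore 30.
- Dropout: 30 / 0.9 = 33.3, rounded up to 34.

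Both stated figures reproduce as a single-endpoint calculation at an undivided 0.05.

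**2. Two primaries at 0.05 each.** Independent case: family-wise error 1 − 0.95² = 9.75%; joint power 0.815² = 66%. For correlated endpoints, bivariate normal test statistics were simulated (2 million draws) with per-endpoint power of 81.5%.

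| Correlation between endpoints | Error if either suffices | Power at N = 30 if both required |
|---|---|---|
| 0 | 9.75% | 66% |
| 0.3 | 9.5% | 69% |
| 0.5 | 9.1% | 71% |
| 0.8 | 7.8% | 75% |

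If either suffices, power is not the problem: the chance of at least one success is 88% to 97%. If both are required, error is not the problem: it is at most 5%.

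**3. How far the joint power depends on the assumptions.**

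- Taking the protocol's 80% at face value for both endpoints: 0.80² = 64% (independent).
- All 34 participants analysed: 0.863² = 74% (independent).
- JPSE power alone at N = 30: 35% at f = 0.15, 56% at 0.20, 75% at 0.25, 81% at 0.27, 99% at 0.40. The document does not say which applies. Only a JPSE effect of about 0.40 would bring joint power to 80% under independence (0.815 × 0.988 = 0.805).
- Repeated-measures correlation: at rho = 0, 0.3 and 0.7, per-endpoint power at N = 30 is 52%, 67% and 96%, so independent joint power is about 27%, 46% and 92%. The plan's own N fits rho = 0.5.

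**4. What keeping two primaries would need (f = 0.27 for both, rho = 0.5).**

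- Alpha split to 0.025 each: N = 30 gives 72.0% power per endpoint. Reaching 80% needs N = 36, or 40 after dropout.
- Both required, independent, 80% joint power: N = 38, or 43 after dropout (44 for equal groups).

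**The case against.** **Success and multiplicity rules are often left to the SAP.** This is fair, and a flat 0.05 level is compatible with a fixed sequence or with requiring both endpoints. The missing rule alone would therefore be a weak point. But the protocol itself claims power for NPRS and JPSE, and a later rule cannot make an NPRS calculation cover JPSE. An alpha split would lower power per endpoint to 72%, and a both-required rule would lower joint power to 66–75%, under the assumptions above.

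**JPSE is not wholly absent.** This also stands in part. If JPSE means cervical repositioning error, specific objective 1 names the construct, and the entry criterion gives a unit (degrees) and a citation. That shows an intention to assess it. It does not supply an outcome definition, a scoring rule or a powering input.

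**Stronger readings the documents do not support.**

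- A reader might infer that the error rate and the power both fail. They do not fail under the same rule.
- A reader might put joint power near 56%. That figure follows from f = 0.25, which is what 2.5 points with SD 2.5 implies (2.5/4 ÷ 2.5), giving 0.753² = 0.567. The protocol states f = 0.27. The gap between 0.25 and 0.27 is a separate matter and should not be counted as a cost of having two endpoints.
- A reader might count 21 outcomes and quote 1 − 0.95²¹ = 66% for at least one false positive. That assumes independence, which the protocol's own HRV definitions contradict: the stress score is computed from SD2, S/PS from the stress score and SD1, and LF/HF from LF and HF. Nor does the protocol present the non-primary outcomes as confirmatory.

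**Conclusion.** The point holds in a limited form. The protocol claims 80% power at two-sided 0.05 for a primary outcome made up of NPRS and JPSE, on inputs for NPRS alone, and with JPSE undefined. If either primary suffices, the 5% error rate is not kept: it is 9.75% for independent endpoints and about 7.8% at correlation 0.8. If both are required, the error rate holds but 80% power is not shown: about 66% to 75% at N = 30.

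The error figures depend only on the correlation between endpoints. The power figures rest on an assumed JPSE effect of f = 0.27 and rho = 0.5, and would change with either. The conclusion is therefore that 5% error together with 80% power is unsupported, not that the trial must be underpowered. For NPRS alone, the stated N of 30 and 34 reproduce at f = 0.27 and rho = 0.5.

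**What to change.** - **Sample size:** name NPRS, the only outcome with sample-size inputs, as the single primary outcome, and limit the power claim to it.
- **Statistical Analysis:** test NPRS by the planned group-by-time interaction at two-sided 0.05. Test JPSE next, at 0.05, only if NPRS is significant. This keeps the error over the two tests at or below 5% with no added participants. Label the remaining outcomes as supportive.
- **Outcome measures:** expand JPSE and state how it is measured and scored, with its unit and time points.
- **Timing:** the Intervention section gives arm sizes of 14 and 17 in the past tense, and Statistical Analysis reports a normality result as already obtained. If data have been collected, date the change and report it as made after collection.

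**Cost.** Mostly protocol wording. No confirmatory JPSE claim is possible if NPRS fails, and the chance of confirming both is the 66–75% above under the same assumptions. If the sponsor needs both as primaries, the alternative is a stated success rule, JPSE inputs and a larger trial: 40 with an alpha split, or 44 if both must succeed, under the assumptions shown.

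### The protocol gives two unreconciled MCIDs for the NPRS, 1.3 and 2.5 points, and sizes the trial on the larger, so its claim of 80% power for the MCID fails if 1.3 applies

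*Protocol*

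**What the plan says.** The Participants section of the protocol, in its item on the Numeric Pain Rating Scale (NPRS), states: "The minimum clinically important difference (MCID) for this tool have been established at 1.3 points". The same sentence puts "the minimum detectable change (MDC) at 2.1 points", for individuals with neck pain, and cites reference 9.

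The Sample size section names the NPRS as a primary outcome, together with JPSE. It says the calculation is "based on the detection differences of 2.5 points in the NPRS (MCID (minimal clinically important difference", citing reference 40, and that this is "estimated for a variance in patients with neck pain of 10 points", "assuming a standard deviation (SD) of 2.5 points". It continues: "Assuming an effect size (F-test) of 0.27 for ANOVA: repeated measures, within-between interaction groups differences", with "an alpha level of .05, and power of 80"%. The result is 30 participants in total, raised to 34 (17 per group) for 10% dropout, with two-sided testing.

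The Statistical Analysis section plans a two-group, two-time-point repeated-measures ANOVA with t tests, a 0.05 significance level and Cohen's d. It refers to neither MCID.

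**The concern.** One protocol attaches the label MCID to two values for the same scale and the same condition. The second is 2.5 / 1.3 = 1.92 times the first. The trial is sized on the larger value under that label, so a reader is told that it has 80% power for the smallest difference that matters.

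If the smaller value is the right one, a true effect between 1.3 and 2.5 points would be clinically important by the protocol's own instrument description, yet could easily miss significance. A null result could then be taken as evidence against an important effect when the design cannot support that reading. While both values stand, the protocol also does not say which one an observed difference on this outcome should be set against.

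**Working it through.** **Inputs.** From Sample size: difference 2.5, SD 2.5, f = 0.27, two-sided alpha 0.05, power 80%, N = 30 before and 34 after dropout. From Participants: MCID 1.3, minimum detectable change 2.1, test-retest ICC 0.76. From Statistical Analysis: 2 groups, 2 time points. The pre-post correlation rho is not given and is an assumption throughout.

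**Reproducing the plan's figure.** For the group-by-time interaction with m = 2 time points, the noncentrality is lambda = f² × N × m / (1 − rho), on 1 and N − 2 degrees of freedom. With f = 0.27, N = 30 and rho = 0.5:

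lambda = 0.0729 × 30 × 2 / 0.5 = 8.75, power 81.5%.

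So 30 is reproduced at rho = 0.5, and 30 / 0.9 = 33.3 rounds up to 34. Other correlations do not give 30: rho = 0 needs 56, 0.3 needs 40 and 0.7 needs 20 (equal groups).

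The stated difference and SD imply f = 2.5 / (4 × 2.5) = 0.25 rather than 0.27. At rho = 0.5 that gives 75.3% power with 30 and 80.7% with 34. This is a side matter and does not affect the point.

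**Power for 1.3 points, SD 2.5 as the SD of the analysed quantity.** Here d = 1.3 / 2.5 = 0.52. With 15 per arm the noncentrality is 0.52 × sqrt(15/2) = 1.42. Two-sided noncentral-t power is:

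- 15 and 15: 28.0%
- 14 and 17 (the group sizes printed under Intervention): 28.6%
- 17 and 17: 31.3%

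Reaching 80% would need 60 per arm. This case is the same as a per-visit SD of 2.5 with rho = 0.5, because the SD of change is 2.5 × sqrt(2 × (1 − 0.5)) = 2.5.

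**Power for 1.3 points, SD 2.5 as the SD at each visit.** Here f = 1.3 / (4 × 2.5) = 0.13, in the same noncentral F:

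| rho (assumed) | N = 30 | N = 34 |
|---|---|---|
| 0 | 16% | 18% |
| 0.3 | 21% | 24% |
| 0.5 | 28% | 31% |
| 0.6 | 34% | 38% |
| 0.7 | 43% | 48% |
| 0.76 | 51% | 56% |
| 0.8 | 58% | 64% |
| 0.9 | 87% | 91% |

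**Using the variance of 10 instead.** An SD of 2.5 has variance 6.25, so the two spread figures in that passage differ. With SD = sqrt(10) = 3.16 for the analysed quantity, d = 1.3 / 3.16 = 0.41, and power is 19.3% (15 per arm) to 21.4% (17 per arm).

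**Precision.** The 95% half-width for the between-group difference at 15 per arm is 2.048 × SD × sqrt(2/15). With SD 2.5 it is 1.87. With a per-visit SD of 2.5 the SD of change is 2.5 × sqrt(2 × (1 − rho)), which gives 1.30 at rho = 0.76 and 1.18 at rho = 0.8.

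**The case against.** A trial may properly be powered for a difference larger than the MCID, and the totals of 30 and 34 reproduce, so there is no arithmetic error in the size. Both points stand. The defect is the label and the power claim that rests on it.

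Three stronger readings are tempting and should not be made.

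- **That 1.3 is right and 2.5 is a mistake.** Each value is cited, one to a randomised trial and the other to a systematic review of the scale's psychometric properties in neck pain. Neither source is at hand. The documents show a contradiction, not which side of it is wrong.
- **That power for 1.3 is simply 28%.** That is one case. The planned test depends on a correlation that the protocol does not state. The nearest figure it offers is the test-retest ICC of 0.76, which is not a four-week pre-post correlation under treatment; taken at face value it would give 51% to 56%. The percentage therefore has to carry its assumption and a range.
- **That a zero estimate could never exclude 1.3.** This holds at a half-width of 1.87, but not once the correlation is about 0.76 or higher.

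It is also fair to say that judging the result against whichever threshold suits is a possible misuse, not something the protocol plans. Its analysis section uses neither MCID.

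**Conclusion.** The point holds as an internal contradiction with a consequence for the stated power. The protocol gives 1.3 and 2.5 as the MCID of one scale in one condition, reconciles them nowhere, and presents its 80% as power for the MCID.

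If 1.3 is the MCID, that claim is not met. With 30 evaluable participants, power is about 28% under the correlation of 0.5 at which the plan's own calculation reproduces (31% with 34). It lies between about 16% and 58% over correlations from 0 to 0.8 with 2.5 as the per-visit SD, and is 19% to 21% if the variance of 10 is used. Only a correlation near 0.9 would restore 80%. The exact figure rests on the SD and correlation assumed; the shortfall does not, short of that extreme. If instead 2.5 proves to be the supportable MCID, the error lies in the Participants section and this power shortfall falls away.

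**What to change.** Go back to the two cited sources, settle one MCID for the NPRS, and use it throughout the protocol.

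- **If 1.3 is kept:** describe 2.5 under Sample size as the target difference, remove the MCID label from it, and give the reason for choosing it. State the power for 1.3 with the SD, what that SD refers to, the assumed correlation, and the range over other plausible correlations.
- **If 2.5 is kept:** correct the figure in the Participants section and say why it was preferred.

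In either case, report the between-group NPRS difference with its 95% confidence interval set against the chosen MCID, so that non-significance is not read as absence of an important effect.

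This is a change of wording and reporting only. Enrolment stays as planned. The cost is a less favourable statement of what the trial can detect if 1.3 is retained.
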